## Abstract

**Background:**

Health promotion is a key process of current health systems. Primary Health Care (PHC) is the ideal setting for health promotion but multifaceted barriers make its integration difficult in the usual care. The majority of the adult population engages two or more risk behaviours, that is why a multiple intervention might be more effective and efficient. The primary objectives are to evaluate the effectiveness, the cost-effectiveness and an implementation strategy of a complex multiple risk intervention to promote healthy behaviours in people between 45 to 75 years attended in PHC.

**Methods:**

This study is a cluster randomised controlled hybrid type 2 trial with two parallel groups comparing a complex multiple risk behaviour intervention with usual care. It will be carried out in 26 PHC centres in Spain. The study focuses on people between 45 and 75 years who carry out two or more of the following unhealthy behaviours: tobacco use, low adherence to the Mediterranean dietary pattern or insufficient physical activity level. The intervention is based on the Transtheoretical Model and it will be made by physicians and nurses in the routine care of PHC practices according to the conceptual framework of the “5A’s”. It will have a maximum duration of 12 months and it will be carried out to three different levels (individual, group and community). Incremental cost per quality-adjusted life year gained measured by the tariffs of the EuroQol-5D questionnaire will be estimated. The implementation strategy is based on the “Consolidated Framework for Implementation Research”, a set of discrete implementation strategies and an evaluation framework.

**Discussion:**

EIRA study will determine the effectiveness and cost-effectiveness of a complex multiple risk intervention and will provide a better understanding of implementation processes of health promotion interventions in PHC setting. It may contribute to increase knowledge about the individual and structural barriers that affect implementation of these interventions and to quantify the contextual factors that moderate the effectiveness of implementation.

**Trial registration:**

ClinicalTrials.gov, NCT03136211.Retrospectively registered on May 2, 2017.

## Background

Chronic diseases represent a huge personal, social and economic burden and one of the greatest challenges for health systems. They are the leading cause of 68% of the deaths at the global level and approximately 42% of these deaths correspond to people younger than 70 years old. It is estimated that around 80% of cardiovascular diseases and 30% of all cancers could be prevented with the adoption of healthy behaviours: a major portion of these diseases is closely related to smoking, unhealthy diet, sedentary lifestyle, and excessive use of alcohol [1]. Likewise, evidence suggests that diet and physical activity level are important modifiable risk factors for depressive and anxiety disorders [2]. Although social determinants of health play a key role, and there is an important social gradient in the prevalence of risk factors, it is an essential issue to develop effective strategies to cope with them especially in people of low socioeconomic status. Thus, health promotion and prevention is a key process of current health systems with the goals of reducing the risk of disease and disability, contributing to an active and healthy ageing and reducing the need for more expensive health care.

Primary Health Care (PHC) is the most accessible and most commonly used health service which provides an integral and continuous care besides, PHC professionals are the major health-care providers for people with multiple morbidities [3]. That is why PHC is the ideal setting for health promotion and prevention interventions [4, 5]. Furthermore, PHC plays a key part in addressing the social determinants of health, mainly through its role in the community, and contributing, in collaboration with other sectors, to the reduction of social inequalities in health [6]. Moreover, as Barbara Starfield points out, to achieve “more effective, more efficient, safer and more equitable” PHC services, the emphasis should shift from treating diseases to caring for individuals and populations [7]. However, the implementation of health promotion and prevention interventions remains suboptimal mainly as a result of work overload and lack of time or training [8–10]. In addition to all these barriers, the most suitable model to approach behaviour change remains unclear, and there is a lack of theoretical basis of interventions, skills in helping people changing behaviour and knowledge of the local context in which these interventions are undertaken [11–13]. Likewise, there are intrapersonal (beliefs, attitudes, knowledge, skills, self-concept, motivation and resources) and interpersonal (health professionals, family and friends) factors which affect PHC users’ receptiveness to health promotion and prevention interventions [9]. One aspect to keep in mind is that a high percentage of people who visit their PHC professionals tend to have confidence with them and their suggestions have a high impact in PHC users’ everyday life [14].

On the other hand, although the majority of the adult population engages two or more risk behaviours, most of the time the approach is carried out separately when multiple interventions might be more effective and efficient. Nevertheless, most of the studies have only focused on a single behaviour so the knowledge about the effectiveness of a multiple approach is still limited. However, there has been a sustained rise in studies evaluating multiple behaviour interventions since 2002 [15, 16]. These studies show that multiple interventions approach comprising education and skills training are associated with small reductions in risk behaviours [15].

Health promotion and prevention interventions are complex and need an in-depth understanding of the context which contributes to its effectiveness. Regarding this, the methodology proposed by the Medical Research Council offers a unique opportunity [17]. This methodology proposes a development in five sequential phases in which both quantitative and qualitative methods are used, which include: a) definition of the theoretical basis (preclinical phase), b) modelling (phase I), c) exploratory trial (phase II), d) definitive randomised controlled trial (phase III) and e) long-term implementation (phase IV). This methodology promotes the participation of citizens and professionals in research and increases the acceptability and the feasibility of intervention. It is also an ideal tool to achieve the sustainability of interventions and the transfer of research to practice. Research on complex interventions marks a turning point in the conventional way of conducting experimental studies in which the most important thing is finding value and understanding the context of practice rather than trying to control its influence. Hybrid trials represent the ideal design because they allow a joint assessment of clinical effectiveness and implementation, thanks to their dual approach [18]. These trials use theoretical frameworks which ensure a systematic and comprehensive way to understand the determinants of implementation as well as its success and impact [19–21].

In this connection, Spanish primary care prevention and health promotion research network (redIAPP) [22] started in 2012 the EIRA study and carried out the first three phases (preclinical phase, phase I and phase II) [8, 9, 23–25]. Currently, the research team is pursuing the phase III through a hybrid trial which aims to evaluatethe effectiveness, the cost-effectiveness and the implementation of a complex multiple risk behaviour intervention to promote healthy behaviours in people between 45 to 75 years attended in PHC. This article describes the protocol for this trial.

### Study objectives and hypotheses

This hybrid trial has the following primary objectives:To evaluate the effectiveness and cost-effectiveness of a complex multiple risk intervention on reducing tobacco use, enhancing adherence to Mediterranean dietary pattern and increasing physical activitylevel in 12 months to baseline compared with usual care.To assess the effectiveness of an implementation strategy in terms of acceptability, adoption, appropriateness, feasibility, fidelity, implementation cost and penetration.

Furthermore, other secondary objectives related to the effectiveness of the intervention will also be evaluated: its impact on reducing cardiovascular and depression risksas well as depressive and anxiety symptoms and incidence of major depression.

We hypothesise that the proportion of people who show a positive behaviour change with regard to any baseline behaviours will be higher among people who receive the intervention than people who receive usual care. We also hypothesise that the intervention will reduce cardiovascular risk, incidence of major depression, depression risk and depressive and anxiety symptoms.

## Methods

### Design

This study is a randomised controlled hybrid type 2 trial with two parallel groups which aims to test a complex multiple risk behaviour intervention of a maximum duration of 12 months and an implementation strategy simultaneously [18]. The protocol of hybrid trial has been written according to the Standards Protocol Items: Recommendations for Interventional Trials (SPIRIT) [26] and the Standards for Reporting Implementation studies (StaRI) [27]. Cost-effectiveness analysis will be conducted following international recommendations [28].

### Study setting

The study will be carried out in PHC centres of seven of the 17 Spanish Autonomous Communities: Andalusia, Aragon, the Balearic Islands, Basque Country, Castile and León, Catalonia and Galicia. Spanish health system which is based on universal coverage with free access for all citizens, is funded by public sources and depends predominantly on the public sector. PHC is provided by multidisciplinary teams (physicians and nurses, paediatricians, social workers and dentists) who perform activities of health care, health education and prevention. Health promotion and community care are included in the basic PHC services; however, there are multiple barriers, like work overload and lack of time or training, that hinder their implementation [8, 9, 29–31].

### Participants

#### EIRA study has two targets

##### PHC centres

The study comprises 26 PHC centres. The criteria for selecting them are: 1) to have internet access; 2) have the possibility of carrying out community activities; 3) to be not located in areas with a huge cultural and linguistic diversity or in tourist areas and 4) to have a highly committed and active management team. All professionals, healthcare professionals and administrative staff, from PHC centres, will be invited to participate voluntarily. Involved professionals must sign a collaboration commitment to the study.

##### PHC users

The study focuses on people between 45 and 75 years who carry out two or more of the following unhealthy behaviours: tobacco use, low adherence to the Mediterranean dietary pattern or insufficient physical activity level. Participants must provide informed consent before any study procedures occur. In addition, they must be registered with a health professional of the PHC centre. They will be excluded if they have advanced serious illnesses, cognitive impairment, dependence in basic everyday activities, severe mental illness, they are included in a long-term home health care program, they are in treatment for cancer or in end-of-life care, or they do not plan to reside in the area during the time that the intervention lasts.

### Intervention

The intervention is based on the Transtheoretical Model (TTM) [32, 33] and will be made by physicians and nurses in the routine care of PHC practices according to the conceptual framework of the “5A’s”: Assess, Advise, Agree, Assist, and Arrange-follow up [34]. It will consist of a first visit of screening in which PHC professional will assess person level of behaviour and stage of change (“Assess”). Behaviours will be assessed by one question to know tobacco use during the last month, two validate questions about the daily consumption of fruits and vegetables [35] and the Brief Physical Activity Assessment Tool [36, 37]. Stages of change will be assessed on the basis of core constructs of the TTM for each of the target behaviours (see Table 1) [32]. Subsequently, the PHC professional will advise the person (“Advise”), will agree with him/her on a realistic set of goals (“Agree”), will assist to anticipate barriers and will develop a specific action plan (“Assist”), and will arrange follow-up support (“Arrange”).

**Table 1 Tab1:** Core constructs of the Transtheoretical Model (Prochaska et al. 2008) [32]

Stages of Change	Description
Precontemplation	No intention to take action within the next 6 months
Contemplation	Intends to take action within the next 6 months
Preparation	Intends to take action within the next 30 days and has taken some behavioural steps in this direction
Action	Changed overt behaviour for less than 6 months
Maintenance	Changed overt behaviour for more than 6 months
Termination	No temptation to relapse and 100% confidence

Intervention is based on the results of previous phases (preclinical, phase I and phase II) [23–25, 38–42]. It will have a maximum duration of 12 months and it will be carried out to three different levels (individual, group and community) according to stages of change and unhealthy behaviour (see Table 2). It will focus on all three target behaviours and PHC professional together with the participant will develop priority actions on one or more of these behaviours.

**Table 2 Tab2:** Description of intervention

	Unhealthy behaviours								
	Tobacco use			Insufficient physical activity			Non-adherence to Mediterranean dietary pattern		
Level of intervention	Individual	Group	Community	Individual	Group	Community	Individual	Group	Community
Stages of change									
Precontemplation	Very brief intervention + SMS			Very brief intervention + SMS			Very brief intervention + SMS		
Contemplation				Brief Intervention + App + SMS	Health education workshops	Social prescribing			
Preparation	Brief Intervention + SMS		Social prescribing				Brief Intervention + App + SMS	Health education workshops	Social prescribing
Action				Very brief intervention + SMS					
Maintenance	Very brief intervention + SMS						Very brief intervention + SMS		
Termination									

*SMS* Short Message Service

Intervention at the individual level has an average intensity between 2 and 3 visits; if necessary, professionals have the freedom to make a greater number of visits. Depending on the stages of change it includes: a) a “very brief intervention” to increase awareness of the need for behaviour change or to support the change and help with relapse prevention; b) a “brief intervention” to make an agreed plan for behaviour change. Health professionals will apply their motivational interviewing skills after following a 20-h online training, an in-person group feedback session and a coded acting patient session [11, 13, 43]. The intervention plan includes the participation in a health education workshop and social prescribing. In addition, the intervention has the support of information and communication technologies, such as a web page addressed to the participant (http://proyectoeira.rediapp.es), the sending of personalised text messages, the use of a mobile app [44] or the recommendation of other gadgets (pedometers, smartwatches, etc).

Group intervention is carried out through two health education workshops focused on healthy diet and physical activity. These workshops are planned to be developed some weeks after initiating the individual intervention and will be conducted by PHC professionals at the health centre. They will take 90–120 min and their purpose is to reinforce the recommendations provided in the individual intervention and to provide people with guidelines that facilitate the practice of physical activity and the adoption of a healthy diet, for example through physical exercise sessions, cooking workshops or preparing seasonal menus.

Community intervention focuses mainly on the social prescribing [45] of resources and activities that are carried out in the community where the participant person resides. Previously every PHC team will identify the community health assets [46] and will choose the most appropriate according to unhealthy behaviours detected, accessibility and the possibility of referral of participants. These interventions will include, for instance, cooking courses, healthy eating workshops, healthy walks, local walking events, line dances, green physical activity programs, etc).

### Usual care

PHC professionals of the control group (usual care) integrate into their practice the recommendations of the Program of Preventive Activities and Health Promotion [47]. This program incorporates preventive protocols that include lifestyle recommendations and a set of preventive activities for a specific age, sex and risk patient groups. Preventive activities are based on systematic screening and brief advice for the prevention of cardiovascular and mental diseases and cancer as well as vaccine recommendations.

### Implementation strategy

The implementation strategy is based on:The “Consolidated Framework for Implementation Research” (CFIR) [19] which identifies five constructs: 1) intervention characteristics (intervention source, evidence strength and quality, relative advantage, adaptability, trialability, complexity, design quality and packaging; and cost); 2) outer setting (patient needs and resources, cosmopolitanism, peer pressure, and external policy and incentives); 3) inner setting (structural characteristics, networks and communications, culture, implementation climate and readiness for implementation); 4) characteristics of individuals (knowledge and beliefs about the intervention, self-efficacy, individual state of change, individual identification with the organisation, and other personal attributes); and 5) the implementation process itself.A set of discrete implementation strategies [20, 48] which includes: plan strategies (gather information, adapt and pilot material and processes, build buy-in, initiate leadership and develop relationships); educate strategies (develop materials, educate, educate through peers, inform and influence stakeholders); finance strategies (modify incentives and facilitate financial support); restructure strategies (revise professional roles and create community and group interventions committees) and quality management strategies (develop and organise implementation monitoring systems, conduct continuous assessment and feedback, establish a system of reminders, obtain and use patient opinion, centralise technical assistance focused on implementation issues).An evaluation framework [21] to determine the effectiveness of implementation through seven implementation outcomes: acceptability, adoption, appropriateness, feasibility, fidelity, implementation cost and penetration.

This implementation strategy will be carried out in three stages, pre-implementation, implementation and post-implementation, further described in Table 3.

**Table 3 Tab3:** Description of implementation strategies

Stage	Key element	Description
Pre-implementation	Barriers and facilitators	During this stage, the scientific literature will be reviewed. Likewise, the researchers will assess local needs, resources, barriers and facilitators to develop specific implementation strategies. Perspectives of clinicians on the internal resources will be measured by the “Survey of Organizational Attributes for Primary Care”.
	Support materials	All the support material for the intervention will be drawn up.
	Management and quality control systems	Mechanisms for the effective communication and the case report form will be defined and piloted. A checklist (on-line database) will be developed and piloted to monitor the progress of implementation in each PHC centre.
	Facilitation and leadership	The facilitator (member of the research team) and the leader (member of the primary care team) of the implementation will be designated.
	Commitment of the stakeholders	Formal compromises will be made with the managers (at the macro, meso and micro levels) and with the professionals of the centres involved and community partners.
	Training	Training activities will be carried out in which training in motivational interview will have a central role
	Collaborative modelling	Local sessions to adapt and tailor the intervention to the specific context trough shares decisions making.
Implementation	Collaborative learning	The facilitator and the leader of implementation will monitor the implementation processes, identify opportunities for improvement and optimise implementation.
	Commitment of main stakeholders	Audit and feedback techniques will be used towards the main stakeholders in order to keep the agreed compromise and the motivation.
	Training	Health professionals will receive continuous training in motivational interview.
Post-implementation	Management and quality control systems	The evaluation of implementation will be carried out through qualitative and quantitative methodologies

### Outcomes

This study distinguishes between three different but interrelated types of outcomes: i) effectiveness, ii) cost-effectiveness and iii) implementation outcomes.

#### i) Effectiveness outcomes

The effectiveness of the complex multiple risk behaviour intervention in comparison with the usual care at maximum 12 months post-intervention will be measured by:
*Primary outcome measures*
Positive change in baseline eating behaviour: adherence to the Mediterranean dietary pattern in low adherence people. For the evaluation, the 14-item Questionnaire of Mediterranean diet adherence (PREDIMED study) will be used [49]. The positive change has been defined as obtaining eight or fewer points at the study entry and nine or more at the end of the study in this questionnaire.Positive change in baseline physical activity behaviour: sufficient physical activity level in insufficiently active people. For the evaluation, the International Physical Activity Questionnaire will be used [50]. The positive change has been defined as having a low physical activity level at the study entry and a moderate or high physical activity levelat the end of the study.Positive change in baseline smoking behaviour: self-reported continuous abstinence [51]. For the evaluation, the interview will be used and optionally the cooximetry. The positive change has been defined as smoking at the study entry and not smoking at the end of the study. We will measure the punctual and continuous abstinence at these two times.

*Secondary outcome measures*
Beginning or making a behaviour change. The proportion of people who are in the stages of action, maintenance or termination according to the TTM at the study entry and at 12 months.Change from baseline on sedentary behaviour. It will be measured by the sitting items from the International Physical Activity Questionnaire.Change from baseline on diet quality. Diet Quality Index-International will be used to determine diet quality [52].Change from baseline on health-related quality of life. It will be measured by the EuroQol-5D questionnaire [53].Reduction of the cardiovascular risk. The proportion of people with low/moderate and high/very high baseline cardiovascular risk who have reduced it. Cardiovascular risk will be calculated using REGICOR [54, 55] and SCORE [56] function charts.Change from baseline on body mass index. Body mass index is defined as the body weight divided by the square of the body height and is expressed in units of kg/m^2^.Change from baseline on waist circumference. The waist circumference will be measured at a level midway between the lowest rib and the iliac crest. It will be expressed in units of cm.Change from baseline on blood pressure. It will be measured in the routine clinical practice by validated electronic monitors and it will be expressed in units of mmHg.Change from baseline on lipid profile. The lipid profile will include: low-density lipoprotein, high-density lipoprotein, triglycerides and total cholesterol. They will be expressed in units of mg/dl.Change from baseline on arterial stiffness. Arterial stiffness will be assessed by the “Cardio-Ankle Vascular Index”. It will be measured by the Vascular Screening System VaSera VS-1500 N or VaSera VS-2000.Change from baseline on theankle-brachial index. It will be measured by the Vascular Screening System VaSera VS-1500 N or VaSera VS-2000.Change from baseline on the “REgicor and Artper Score fOr aNkle brachial index (REASON)” [57].Change from baseline on the perceived functional social support. The questionnaire Duke-UNC-11 will be used to determine the perceived functional social support [58–60].Reduction of the incidence of major depression will be evaluated by CIDI interview [61].Reduction of the risk of depression in participant non-depressed at baseline. Risk of depression will be calculated using the algorithm PredictD [62].Reduction of depression symptoms. The Patient Health Questionnaire-9 will be used to determine the prevalence and the severity of depression symptoms [63].Reduction of anxiety symptoms. The General Anxiety Disorder-7 questionnaire will be used to determine the prevalence and the severity of anxiety symptoms [64].Change from baseline on unhealthy behaviours of professionals of the PHC intervention centres.

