### Sample size

The sample size was calculated on the basis of data from the literature and some results of phase II. We expect a difference in the percentage of people who show a positive change in one or more of the three behaviours between the two groups of at least 8%. Assuming 30% patient loss to follow-up, alpha risk of 5%, beta risk of 20%, and an intracluster correlation of 0.01 [68], we consider that it is necessary to study a minimum of 140 participants for each PHC centre, a total of 3640 people (1820 for each of the two groups, 13 PHC centre per group). PASS software was used to compute the sample size [PASS 14 Power Analysis and Sample Size Software (2016). NCSS, LLC. Kaysville, Utah, USA, ncss.com/software/pass]. Sampling was done in order to fulfil an established sex and age quota which is proportional to the last general population census.

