At PHC centre level, we will collect information related to: assigned population (total number; average age; distribution by age group and sex; percentage of immigrants; deprivation index; prevalence of tobacco use; level of physical activity and number of people allocated to home care), organisational structure (population coverage; average attendance; number of physicians, nurses and social workers; accreditation as training health centre; participation in undergraduate and postgraduate training; average visits per day; population per health professional; average time per visit and participation research experience). We will also measure the PHC centres’ internal resources for change by the “Survey of Organizational Attributes for Primary Care” [70].

At the professional level, personal data will be collected (age, sex, academic education and experience in PHC). PHC professionals will have to complete a self-administered questionnaire. This questionnaire collects information about professionals’ behaviours with reference to tobacco use, daily consumption of fruit and vegetables and level of physical activity. In addition only in health professionals of intervention centres, it includes nine items to measure the perception of appropriateness and acceptability of the intervention; these items are based in questionnaires which measure similar constructs [71].

Participant-level data are described in Table 4. Recruitment, first screening for entrance to the study and intervention visits will be done by health professionals. Data collection at participant level will be supported by an external unit of local trained personnel who will carry out two visits (baseline and at the 12 months) in each PHC centre because they are not considered as usual care tasks. Data will be collected by means of an online CRF specially designed for the study. This CRF will be pilot tested in pre-implementation stage (see Table 3). The management of the study is based on a central coordination unit, a regional coordination unit and a PHC coordination unit using different periodic communication methods (meetings, teleconferences, e-mails, etc.).

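### The diet and physical-activity primary outcomes use only a crossing of the baseline cut-off, and the graded scores from the same two instruments are not outcomes at all

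*Protocol article*

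**What the plan says.** Under Outcomes, i) Effectiveness outcomes, the diet responder rule reads "The positive change has been defined as obtaining eight or fewer points at the study entry and nine or more at the end of the" trial. For physical activity it is "having a low physical activity level at the study entry and a moderate or high physical activity" level at the end. Neither rule sets a minimum change.

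Data collection and management assigns both readings to an external unit "who will carry out two visits (baseline and at the 12 months) in each PHC centre", and Table 4 shows no repeat baseline or confirmatory reading.

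The secondary outcomes include many graded measures. For diet, however, they name a different index (the Diet Quality Index-International), and from the activity questionnaire they take only the sitting items. The two primary instruments therefore enter the outcome list only as crossings.

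The trial is sized on the proportion of "people who show a positive change in one or more of the three behaviours between the two groups of at least 8" percentage points. The Analysis section already foresees hierarchical linear and logistic models.

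**The concern.** The diet cut-offs are adjacent integers. A participant who goes from 8 to 9 is a full success; one who goes from 4 to 8 has gained four points and counts as unchanged. Likewise, activity gained within the low category counts for nothing. The rule ignores how far anyone moved and how far they started from the cut-off.

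What is at stake is precision and interpretation. If the intervention shifts diet or activity modestly across the whole group, the responder proportions pick up only part of that shift. The outcome list offers no graded result from the same instruments against which to check a null finding.

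**Working it through.** **Plan's own figures.** The article gives no score distribution, reliability or control response rate, so it has no figure on this point to reproduce. The sample size is not in conflict with it. 26 × 140 = 3640 enrolled, and 140 × 0.70 = 98 completers per centre. With 46% against 54%, two-sided 5% (assumed), 80% power and an intracluster correlation of 0.01, the required total is 3328, or 3588 with a continuity correction.

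**Assumed inputs for the diet score.** SD 2; mean 6 to 8; 12-month correlation r of 0.5 to 0.8; scores rounded to integers from 0 to 14; participants restricted to 8 or fewer at baseline; true gain 0.3 points in the intervention arm.

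**Efficiency formula.** Efficiency is the ratio of squared effect to variance:
- binary: (p1 − p0)² / [p0(1 − p0) + p1(1 − p1)]
- baseline-adjusted score: δ² / (2σ²), where σ² is the variance of the 12-month score left after adjusting for baseline.

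**Worked case, mean 7, r = 0.7.**
1. Responders are 12.2% without effect and 16.2% with a 0.3-point gain, a difference of 0.0401 before rounding. Binary: 0.0401² / (0.1071 + 0.1358) = 0.00662.
2. On the continuous scale the residual variance is 2² × (1 − 0.7²) = 2.04; rounding to integers raises it to about 2.16. Adjusted score: 0.3² / (2 × 2.16) = 0.0208.
3. Efficiency: 0.00662 / 0.0208 = 0.32.

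**Cross-check with a 0.5-point gain, same inputs.** Responders are 12.2% against 19.3%. The required size per arm, ignoring clustering, is 407 for the crossing rule, 202 for the raw 12-month mean and 136 for the baseline-adjusted mean. 136 / 407 = 0.33 and 202 / 407 = 0.50.

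**Range.** Over means 6 to 8 and r 0.5 to 0.8, with a 0.3-point gain, efficiency against the adjusted score runs from about 0.17 (mean 6, r 0.8) to about 0.52 (mean 8, r 0.5). Against an unadjusted comparison of means, over a similar range of assumptions, it is about 0.32 to 0.61.

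**What that means for power.** Assume 80% of completers are at risk on diet: 98 × 13 × 0.8 = 1019 per arm, about 78 per centre. The design effect is 1 + 77 × 0.01 = 1.77, so the effective size is 1019 / 1.77 = 576. In the worked case:
- binary: √(576 × 0.00662) − 1.96 = −0.01, about 50% power
- adjusted score: √(576 × 0.0208) − 1.96 = 1.50, about 93% power.

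For means 6 to 7 the ranges are 34% to 54% against 82% to 98%.

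**Baseline score in the binary model.** Adding it to the logistic model for diet raises the information on the treatment effect by about 5% to 19% under the same assumptions.

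**Activity.** If the category is treated as a cut of one normal underlying scale, with 40% to 70% low at baseline, r 0.5 to 0.8 and a shift of 0.15 SD, efficiency is about 0.28 to 0.59 of the adjusted comparison. This is rougher than the diet figure.

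**The case against.** The strongest reply is that the responder rule fits the question. The objectives concern people with poor diet or low activity reaching an acceptable level, the planned number needed to treat requires a binary outcome, and the trial is sized on a binary composite. All of this stands, and it is why the responder outcomes should stay primary. It is also fair that covariates are often left to an analysis plan, which is not shown. The outcome list, however, is set out in this article, and the graded scores are not on it.

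Several stronger inferences are tempting, and the documents do not support them:

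- **Bias from regression to the mean.** It raises the response in both arms equally in expectation, because centres are randomised. It does not itself bias the comparison or inflate type I error. Eligibility is also screened with other instruments ("two validate questions about the daily consumption of fruits and vegetables [35] and the Brief Physical Activity Assessment Tool"); regression to the mean enters because the outcome conditions on the baseline reading.
- **Most responders are noise.** With no true change, the assumed inputs give 5% to 27% diet responders. That range is wide, none of its inputs is in the article, and a 12-month correlation mixes measurement error with real change.
- **The background rate undermines the 8-point difference.** With 1274 completers per arm and design effect 1 + 97 × 0.01 = 1.97, power is 82% at 46% vs 54%, 87% at 28% vs 36%, and 92% at 20% vs 28%.
- **The effect rests mainly on people next to the cut-off.** Those at exactly 8 carry about 26% to 56% of it, and in most scenarios half or less.
- **A minimum gain would cure the problem.** Requiring 2 points cuts no-effect responders from 12.2% to 8.0% (mean 7, r 0.7), but the required size rises from 407 to 428 per arm.

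The 0.3-point gain is also an illustration, not a design value. For means 6 to 7 it moves diet responders by only 2.4 to 4.2 percentage points, whereas the 8 points refer to the any-of-three composite.

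**Conclusion.** The point holds as one of efficiency and interpretation, not validity. The article makes the diet and activity primary outcomes single-reading crossings and names no graded outcome from either instrument. For diet, the crossing keeps roughly 0.2 to 0.5 of the efficiency of the baseline-adjusted score. This rests on an assumed SD of 2, mean of 6 to 8, correlation of 0.5 to 0.8 and a 0.3-point shift; the loss is smaller against an unadjusted mean. For activity the loss is likely substantial too, but depends on a cruder model. The consequence is limited: a null responder result could not be told apart from a real but modest shift using the outcomes now listed. A reader should not infer that the primary comparison is biased, or that the trial is underpowered for its own 8-point target.

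**What to change.** Keep the responder definitions as primary and make two changes.

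1. In the secondary outcomes, add the 12-month total of the 14-item Mediterranean diet questionnaire and 12-month total activity from the International Physical Activity Questionnaire, labelled as supportive. Compare them between arms in the hierarchical linear model already planned, adjusted for the baseline value, in the same participants who are at risk on that behaviour. Report them beside the responder results. The scale for total activity can be settled in the analysis plan.
2. In the Analysis section, name the baseline score as a prespecified covariate in the binary diet and activity models.

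A sensitivity analysis requiring a gain of at least 2 diet points is optional and should not be presented as restoring power.

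Both changes use data already scheduled at the baseline and 12-month visits. The cost is some wording, a few extra models and two more secondary outcomes to report.
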